**Methods/design:**

PHEDRE (Pharmacodépendance Et DREpanocytose-drug dependence and sickle-cell disease) is an observational, descriptive and transversal study. Patients under the age of 26 with sickle-cell disease are included in the study by the doctors looking after them in sickle-cell disease centres. The patients are then contacted by a trained researcher for a telephone interview, including an evaluation of the Diagnostic and Statistical Manual of Mental Disorders criteria for abuse and dependence to equimolar mixture of oxygen and nitrous oxide and for each of the analgesic drugs taken by the patient. The data are also completed using the subject’s medical record.

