Sickle-cell anaemia and severe SCD are haemoglobinopathies from the group of corpuscular hereditary haemolytic anaemias. In France, patients with SCD are managed via a patient-oriented care network, especially Reference Centres or Special Centres for Children and Adults (RSCCA). These centres are scientific and clinical excellence structures for rare diseases such as SCD. The RSCCA medical practitioners see each patient, regardless of their age, at an inpatient/or outpatient consultation, at least once per year as part of routine follow-up. The acute pain caused by Vaso-Occlusive Crises (VOC) are the most common clinical symptom and the first cause that lead to the emergency department for children, adolescents and adults with SCD. Patients are also prone to chronic or recurrent acute pain, that require analgesics taken at the patient’s home. This pain is subject to significant inter-individual variability but also intra-individual variability, as much in terms of severity, site and duration of the pain episode [20, 21]. The unforeseeable nature of the pain and extent of the active pain relief strategies (called coping strategies), developed by patients with SCD, are different from other painful disorders in which similar analgesic treatment is used, and imply the difficulties patients and health care professionals experience in managing it [21, 22]. According to the intensity of the pain and type of treatment and according to the World Health Organisation’s (WHO) classification, level I analgesics, (acetaminophen and Non-Steroidal Anti-Inflammatory drugs (NSAIDs)), level II (codeine, tramadol, nalbuphine) and level III (morphine) can be used. EMONO is ideal for the rapid management of pain and/or in combination with morphine in hospital in children and adolescents [21, 23]. One of the barriers to management of pain in patients with SCD is the reticence of health care professionals to use morphine-based analgesics, for fear of the patient developing drug dependence [21]. Indeed, the request for analgesics can be perceived, not as a response to the pain episode but as a drug addiction [24, 25], whereas most often it is a simple clinical impression [26]. Nevertheless, undertreated pain exposes patients to the risk of “pseudo-addiction”, which occurs when patients attempt to obtain a stronger analgesic dose, thus possibly coming across resistance from the nursing team. These behaviours, which look like the compulsive search for analgesic drugs, are interpreted as being addictive-like-behaviour and widely keep the beliefs of the healthcare team as to the dependence of their patients. However in pseudo-addiction, analgesic-seeking behaviour stops when the pain is treated effectively and does not persist after pain relief has been achieved [27]. Evaluation of the use of analgesic drugs, on the basis of Diagnostic and Statistical Manual of Mental Disorders (DSM) criteria for substance abuse and dependence [28], makes it possible to differentiate the symptoms occurring only in a context of pain, in the aim of managing the pain, and thus describing pseudo-addiction (common), from symptoms also occurring when there is no/mild pain, and more in favour of true addiction (rarer). The major risk is that these patients who, in order to deal with their pain, demonstrate behaviour compatible with substance use disorder criteria, receive fewer analgesics and in whom therefore treatment is not optimal [29–31]. Also, if genuine drug addiction to analgesics was identified, it would require treatment adjustment. A specific evaluation is therefore necessary in order to improve patients’ management. The role of EMONO and opiate analgesics in the treatment strategy, the potential for abuse and dependence to which is well known, today require special monitoring of the risk of overconsumption, abuse and dependence in this population.

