### Telephone interview

When Nantes CEIP-A receipts the inclusion form and written consent, the trained researcher schedules a telephone interview with the patient. Telephone interview is carried out with a trained researcher from Nantes CEIP-A. The interview is suited to the child’s, adolescent’s or young adult’s age, maturity and comprehension skills. During the telephone interview, data are stored in the electronic case report form (e-CRF). The following parameters are evaluated during the telephone semi-structured interview for EMONO, and for other analgesic drugs, during pain episodes and outside pain episodes:*Prevalence of problematic use*:

Problematic use is abuse of or dependence on a substance according to the fourth edition of DSM (DSM-IV), and substance use disorder according to the fifth edition (DSM 5). At the time the protocol was written, we used DSM-IV criteria because the DSM 5 was not yet translated in French. The DSM-IV identifies seven substance dependence diagnostic criteria and four substance abuse diagnostic criteria. Abuse is defined by at least one of the four DSM-IV criteria of substance abuse and drug dependence by at least three of the seven DSM-IV criteria of substance dependence.2.*Description and characterisation of problematic use:*

Consumption will be evaluated on the basis of quantitative and qualitative responses on the effects sought, quantitative and qualitative responses to each substance abuse and dependence criterion, by separating the pain-related criteria and non-pain-related criteria and quantitative and qualitative responses on craving.3.*Study of the relationships between problematic use and the other study evaluation parameters*

The outcome measures are sociodemographic, clinical and therapeutic data and data on consumption of other psychoactive substances, and their relationship with problematic use of analgesic drugs. This study will be used to demonstrate any factors relating to problematic use of analgesic drugs, or even a specific analgesic drug.

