### Statistical methods

All evaluation parameters will be subjected to a descriptive analysis. The quantitative variable evaluation parameters will be described using position parameters (mean or median) and dispersion (standard deviation, interquartile range, range). Normality of their distribution will be assessed (normality test and evaluation using the relevant graphic tools). The qualitative variable evaluation parameters will be shown in the form of number and frequency tables for each modality. The primary outcome measure will be evaluated by the frequency of subjects with EMONO problematic use compared to the overall study population. The secondary outcome measures will be assessed by the frequency of subjects demonstrating problematic use of one or several other analgesic drugs, compared to the overall study population, by estimating the occurrences of positive responses for the various effects sought when taking analgesic drugs, for each DSM-IV substance abuse and dependence criterion, for each pain-related criterion, and non pain-related criterion (if the DSM-IV substance abuse and dependence criteria are met), and for craving. The frequencies will be estimated for EMONO and for each of the other analgesic drugs, the use of which is identified as problematic. The relationships between problematic use of analgesic drugs (EMONO and/or others) and the other study evaluation parameters will be assessed by univariate analysis and the appropriate statistics tests, depending on the type of variable and the size of the study population (parametric or non-parametric tests). The existence or absence of problematic use can then be studied as a dependent variable in a multivariate analysis (i.e. logistic regression) in order to test the relationship with independent variables selected from the previous analysis. No intermediate analysis or subgroup analysis is to be carried out in this study*.*

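### Counting dependence criteria separately for each drug can leave a patient whose criteria are spread over several level II/III analgesics as a non-case; a pooled sensitivity result would show how many

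*Protocol article*

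**What the plan says.** Under Telephone interview, the Protocol article defines problematic use as abuse of, or dependence on, a substance by DSM-IV. There are two routes to it. For abuse, one criterion out of four is enough; for dependence the rule is "drug dependence by at least three of the seven DSM-IV criteria of substance dependence". That sentence does not itself say whether criteria are counted per drug or over drugs. Two other places settle it:

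- The Abstract (Methods/design) has the criteria evaluated for EMONO and "for each of the analgesic drugs taken by the patient".
- Statistical methods defines the patient-level secondary outcome as the "frequency of subjects demonstrating problematic use of one or several other analgesic drugs", and adds: "The frequencies will be estimated for EMONO and for each of the other analgesic drugs".

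The patient-level result is thus a union of per-drug verdicts. Nowhere are criteria pooled before the threshold is applied. The first secondary objective nevertheless asks about WHO level II and III analgesics other than EMONO as a group, and Background names four of them: "level II (codeine, tramadol, nalbuphine) and level III (morphine) can be used". Patient recruitment asks the patient to list every analgesic of the past 12 months, at home and in hospital, so several drugs per patient are foreseen.

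**The concern.** A threshold of three, applied within each drug, depends on how a patient's criteria are distributed over drugs as well as on how many there are. Two criteria on one analgesic plus one different criterion on another make three in all, yet neither drug reaches three. With no abuse criterion on any of these drugs, that patient is not a problematic user of level II/III analgesics.

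Two results are exposed. The first is the prevalence for the first secondary objective. Relative to a pooled rule the error can go only one way, because a patient with three criteria on one drug always has at least three when drugs are pooled. The second is the association analysis, where the same yes/no variable is the dependent variable. A patient on one level II/III analgesic can never be lost this way and a patient on two or more can, so the misclassification is tied to the number of drugs used. That is a therapeutic variable of the kind the third secondary objective examines, so an association with it could be distorted and not merely diluted.

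**Working it through.** There is no figure in the plan to reproduce: Study size states that no sample size was calculated, and no expected prevalence is given. The check is of the counting rule.

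**Inputs from the document.** Dependence at 3 or more of 7 criteria; abuse at 1 or more of 4 (Telephone interview). Four level II/III drugs named (Background).

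**Assumptions, because the document gives no figures.** *k* is the number of distinct dependence criteria a patient meets over all level II/III analgesics, *m* the number of those drugs used, and *q* the chance that a criterion is endorsed for a given drug. All percentages are shares of patients with that *k* and *m*, not of the study population.

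**Step 1: no overlap, no abuse criterion.** Each criterion falls at random on exactly one drug. The share missed is the share of the m^k allocations in which no drug reaches three.

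- k = 3: missed = 1 − m/m³ = 1 − 1/m². Two drugs: 1 − 1/4 = 75%. Three drugs: 1 − 1/9 = 89%. Four drugs: 1 − 1/16 = 93.8%.
- k = 4: missed = 1 − m[4(m − 1) + 1]/m⁴. Two drugs: 1 − 10/16 = 37.5%. Three drugs: 1 − 27/81 = 67%. Four drugs: 1 − 52/256 = 79.7%.
- With two drugs nothing is missed from k = 5 upwards, since one drug must then hold at least three. With three drugs the same holds at k = 7. With four drugs 15.4% are still missed at k = 7 (enumeration).

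**Step 2: overlap.** Let each criterion be endorsed independently for each drug with chance q, given that it is endorsed for at least one. For two drugs put D = 1 − (1 − q)², r = q/D (endorsed for a given drug) and s = q²/D (endorsed for both). For k = 3, missed = 1 − (2r³ − s³). At q = 0.5, r = 2/3 and s = 1/3, so missed = 1 − (16/27 − 1/27) = 12/27 = 44%. The four-drug values are simulated.

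| q | k = 3, two drugs | k = 3, four drugs |
|---|---|---|
| 0.25 | 63% | 81% |
| 0.5 | 44% | 50% |
| 0.75 | 19% | 10% |
| 0.9 | 4.5% | 0.5% |
| 1 | 0% | 0% |

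**Step 3: the abuse route.** A patient with one abuse criterion on any level II/III drug is a case whatever the dependence count. If a share *a* of the patients concerned has one, independently of the split, the loss is multiplied by (1 − a). At a = 0.5 and k = 3 the no-overlap figure falls from 75% to 37.5% (two drugs) and from 93.8% to 46.9% (four drugs).

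**Step 4: what pooling changes.** If three-of-seven is applied to the union of criteria, everyone with k of 3 or more is counted. The abuse rule is unchanged by pooling, because its threshold is one.

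**The case against.** The strongest reply is that scoring by drug suits this study. Its stated purpose is to monitor the risks of particular products and to look for factors linked to analgesics, or even to one specific analgesic. The definition refers to a substance, and the union over drugs already gives a patient-level result. This stands, and it is why the per-drug analysis should remain the main one.

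A second reply is that the article leaves derivation rules to the full protocol or analysis plan. That would answer a complaint that a rule is missing. Here the article does state the unit of evaluation and the patient-level count, and together they fix a rule with a known blind spot.

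Third, pooling costs specificity. Background's worry is that patients in pain are wrongly taken for addicted, and three criteria are easier to reach over four drugs than on one. This also stands. It argues for a sensitivity result separated by pain context, and against replacing the main outcome.

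A reader might go further and infer that the plan will miss opioid dependence in most patients who move between drugs. The document does not support that:

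- It defines no outcome called opioid dependence.
- It says the analgesic levels can be used according to pain intensity and type of treatment. It does not say that movement between level II and III drugs is routine.
- Switching alone does not split criteria, since one criterion can be endorsed for several drugs.
- The answers for each drug and each criterion are collected and described, so the information is not lost. It is only absent from the case definition.

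**Conclusion.** The point holds in limited form. Read together, the Abstract, Telephone interview and Statistical methods apply three-of-seven within each analgesic and then take the union of the verdicts. A patient with three or more dependence criteria in all, fewer than three on each level II/III drug and no abuse criterion on any is a non-case for the first secondary objective. The same patient is a non-case in the association analysis, unless EMONO use is problematic, since that analysis counts EMONO and/or other analgesics.

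The EMONO primary outcome concerns one product and is unaffected.

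The size is unknown. For three criteria and two drugs the loss lies between 75% of such patients and zero. The upper figure rests on random attribution of each criterion to a single drug and on no abuse criterion being met. The document gives no drugs per patient, criterion counts or overlap, so neither end can be called likely. It would be wrong to read 75% as an understatement of the reported prevalence: it applies only to patients with that pattern, whose number is not known. This is a cheap improvement to a secondary analysis and does not invalidate the design.

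**What to change.** Keep the per-drug results and the outcome of problematic use of one or several drugs as the main analysis. Pre-specify the following beside it:

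1. A class-level sensitivity variable: a dependence criterion counts as met if it is met on any level II/III analgesic, and three-of-seven is applied to that union. The abuse rule needs no change.
2. The same result split by pain-related and non-pain-related criteria, so that pooling does not blur pseudo-addiction with dependence.
3. The number of subjects positive only at class level. If it is near zero, the per-drug rule is shown to lose little.
4. The regression repeated with the class-level outcome as a sensitivity analysis.

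The cost is one derived variable, a few table rows and one extra model run. No interview item is added, because answers are already taken for each drug and criterion. The drawback is that the pooled prevalence is equal to or higher than the per-drug figure and is less specific. It must be labelled as a class-level figure and not as dependence on any one product.

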### Bias

The main potential bias in this study is the heterogeneity bias during data collection. It has been prevented by the choice of a single evaluator.

### Study size

This study has never been driven among children and teenagers with SCD, which is a rare disease.

For this reason, and considering the low number of patients with SCD in France, we planned to include all those who meet the inclusion criteria in RSCCA that agreed to participate in the study. Then, we did not calculate a sample size. Before the beginning of the study, the partner CEIP-A were asked to assess the number of patients fulfilling the inclusion criteria, at their local level, in the RSCCA that agreed to participate. The total number of patients who could potentially be included in France was thus estimated at around 2000 people.

As the RSCCA medical practitioners see each patient at least once per year as part of routine follow-up, the period of inclusion was set at 12 months, to ensure that the study would be proposed to all eligible patients.

### Statistical methods

All evaluation parameters will be subjected to a descriptive analysis. The quantitative variable evaluation parameters will be described using position parameters (mean or median) and dispersion (standard deviation, interquartile range, range). Normality of their distribution will be assessed (normality test and evaluation using the relevant graphic tools). The qualitative variable evaluation parameters will be shown in the form of number and frequency tables for each modality. The primary outcome measure will be evaluated by the frequency of subjects with EMONO problematic use compared to the overall study population. The secondary outcome measures will be assessed by the frequency of subjects demonstrating problematic use of one or several other analgesic drugs, compared to the overall study population, by estimating the occurrences of positive responses for the various effects sought when taking analgesic drugs, for each DSM-IV substance abuse and dependence criterion, for each pain-related criterion, and non pain-related criterion (if the DSM-IV substance abuse and dependence criteria are met), and for craving. The frequencies will be estimated for EMONO and for each of the other analgesic drugs, the use of which is identified as problematic. The relationships between problematic use of analgesic drugs (EMONO and/or others) and the other study evaluation parameters will be assessed by univariate analysis and the appropriate statistics tests, depending on the type of variable and the size of the study population (parametric or non-parametric tests). The existence or absence of problematic use can then be studied as a dependent variable in a multivariate analysis (i.e. logistic regression) in order to test the relationship with independent variables selected from the previous analysis. No intermediate analysis or subgroup analysis is to be carried out in this study*.*

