
Currently there are no data available in France on this concern, and no studies have been carried out in children or adolescents with SCD. This lack of data is all the more significant when we know that childhood experiences and those in adolescence can determine emotions and behaviours and strategies for adaptation to events in adulthood. The main objective of this study is to evaluate the prevalence of problematic use of EMONO in a population of subjects with severe SCD treated in RSCCA in France. The secondary objectives are:To evaluate the prevalence of problematic use of other WHO level II and III analgesic drugs used in the treatment of pain in patients with SCD treated in RSCCA in France.To describe and to characterize problematic use of EMONO and other analgesic drugs.To study the relationships between the existence of problematic use of analgesic drugs (EMONO and/or other analgesics) and the other study evaluation parameters (sociodemographic, clinical and therapeutic data and consumption of other psychoactive substances).

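### Candidate factors are screened and then tested on the same data, so a false factor is likely if candidates are many; the results can explore factors but not demonstrate them

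*Protocol article*

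**What the plan says.** The third secondary objective (protocol article, Background) relates problematic use of analgesics to whole domains of variables: "sociodemographic, clinical and therapeutic data and consumption of other psychoactive substances". The Statistical methods section sets out two steps. First, these relationships "will be assessed by univariate analysis and the appropriate statistics tests, depending on the type of variable and the size of the study population". Second, "The existence or absence of problematic use can then be studied as a dependent variable in a multivariate analysis (i.e. logistic regression"), and the purpose of that model is stated as "in order to test the relationship with independent variables selected from the previous analysis". Both steps use the same patients. The second is permitted rather than required, and the outcome pools EMONO with the other analgesics.

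The Telephone interview section describes the aim in stronger terms: "This study will be used to demonstrate any factors relating to problematic use of analgesic drugs, or even a specific analgesic drug".

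On numbers, the Study size section says "The total number of patients who could potentially be included in France was thus estimated at around 2000 people" and "Then, we did not calculate a sample size". The article gives no expected prevalence, expected number of cases or count of candidate variables.

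**The concern.** The method is stated, so this is not a detail left for the analysis plan to supply. An analysis plan that followed the text faithfully would choose variables because they look associated with the outcome, then test them again on the data that made them look associated. The final p-values and intervals would carry no trace of that choice. Because the candidates are whole domains, many tests are run and chance findings accumulate. Whether a variable is adjusted for would also depend on its unadjusted association, which is a poor guide to confounding.

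At stake is the credibility of the list of factors. The Background section names undertreatment of patients whose behaviour resembles addiction as the major risk. Spurious factors reported as demonstrated would not help that group.

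**Working it through.** There is no planned figure to reproduce: no sample size calculation, power, alpha or event count is stated. The count of about 2000 is a head count of potentially eligible patients and so an upper bound.

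**Assumptions.** Candidate variables: 10 to 30. Entry threshold: p<0.20. Final test: 5%. Prevalence: 2% to 30%. Patients: 500 to 2000.

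**1. Chance of at least one false factor.** For k independent null variables tested at 5%, this is 1 − 0.95^k.

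- k = 10: 1 − 0.599 = 40%
- k = 20: 1 − 0.358 = 64%
- k = 25: 1 − 0.277 = 72%
- k = 30: 1 − 0.215 = 79%

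Neither the number of patients nor the number of cases enters this formula. Two simulations of the two-step procedure (screen at p<0.20, then logistic regression at 5%) agree with it:

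- With 20 independent candidates, 19 of them null, at least one null variable was significant in 60 to 65% of runs at every size and prevalence tried. The formula for 19 gives 62%.
- With 25 null candidates the range was 67 to 75%.

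**2. How much of this is due to the screen.** Without screening, with all variables in one model, the figures were 62 to 67% (20 candidates) and 70 to 75% (25 candidates). The screen does not raise the study-wide rate, and removing it alone would not lower it.

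**3. What the screen does to retained p-values.** If a null variable is kept only when p<0.20, and its adjusted p-value is close to its unadjusted one, it is significant at 5% with probability about 0.05 / 0.20 = 25%. In the 20-candidate simulation the figure was 24 to 27%. A reader of the final table would take this to be 5%.

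**4. What the screen does to confounders.** In a simulated scenario built so that a true confounder had a masked marginal association, the screen dropped it in 74 to 83% of runs. This shows that the mechanism works; it does not show how often it would occur in these data.

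**5. Odds ratios among significant results.** Cases = patients × prevalence. The true odds ratio was 1.30 per standard deviation, and the last column is the geometric mean of the estimates that reached significance after screening.

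| Patients | Prevalence | Cases | Odds ratio when significant |
|---|---|---|---|
| 500 | 2% | 10 | 2.40 |
| 500 | 5% | 25 | 1.75 |
| 2000 | 2% | 40 | 1.54 |
| 500 | 10% | 50 | 1.51 |
| 2000 | 5% | 100 | 1.36 |
| 500 | 30% | 150 | 1.37 |
| 2000 | 10% | 200 | 1.31 |
| 2000 | 30% | 600 | 1.30 |

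Inflation depends on the number of cases, which the article leaves open over a range of about 10 to 600 under these assumptions.

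**6. Effect of a short fixed list.** Six variables: 1 − 0.95^6 = 1 − 0.735 = 26% (simulated 24 to 28%). Three variables: 1 − 0.95^3 = 1 − 0.857 = 14%.

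**The case against.** The case on the other side is substantial. The regression is optional and serves the third secondary objective of a study that calls itself observational and descriptive. The Background section words that objective neutrally, as studying relationships, so the stronger verb in the Telephone interview section may be no more than loose phrasing. The entry threshold and covariate list normally sit in the full protocol or analysis plan, neither of which is shown, and nothing in the article forbids forcing a variable into the model. All of this stands. It limits the weight of the point and means that the absent threshold and list are not criticised here. It does not remove a selection-then-test sequence that the text itself prescribes.

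A reader might infer three stronger claims that the documents do not support.

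- *That few cases are expected.* No prevalence is given. The case definition is broad, since one abuse criterion suffices; pain-driven behaviour is called common and is not excluded from the count; and drugs are pooled. Few cases are plausible if recruitment is low or a single drug is modelled, but that is an assumption.
- *That the false factors come from few cases or from the screen.* Steps 1 and 2 show that they come from the number of variables tested.
- *That screening is what turns modest odds ratios into large ones.* With 600 patients and 5% prevalence (30 cases), a single unscreened test of a binary predictor with true odds ratio 1.7 already averages about 2.66 when significant. That is the ordinary effect of reporting only significant results in a small sample.

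**Conclusion.** The point holds as a moderate one that should be corrected; it does not threaten the primary prevalence estimate. The plan selects and tests on the same data, and the Telephone interview section claims more than that method can deliver. With 20 to 25 candidates and 5% tests, at least one false factor is expected in roughly 60 to 75% of studies, whatever the number of cases. Nominal p-values of retained variables are too small (about 25% rather than 5% for a null survivor of a p<0.20 screen), and a masked confounder can be lost. Inflated odds ratios are conditional: marked below about 50 cases and negligible from about 200, for a true odds ratio of 1.30 per standard deviation.

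The number of candidates, both thresholds, independence between candidates and the prevalence are assumptions. Correlated candidates would change the percentages, but selection would still go unaccounted for in the final p-values.

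**What to change.** In the Statistical methods section, replace univariate selection with a short adjustment set fixed before database lock and ranked by priority. One example is age, sex, genotype or severity, yearly painful crises or admissions, exposure to the drug, and other substance use.

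Let the number of cases observed decide how far down the ranking the model goes. At about one parameter per 10 cases, 30 cases would allow three parameters (30 / 10), so the six-variable list could not be used in full. The ranking is therefore needed.

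Report odds ratios with confidence intervals, using penalised (Firth) estimation if cases are few. Firth reduces small-sample bias but does not remove the inflation that comes from highlighting only significant results, so all entered variables should be reported. Keep the univariate tables as description. Label the analysis exploratory, and in the Telephone interview section change *demonstrate* to *explore*.

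The cost is a few sentences and a standard software option. The downside is that some candidate variables will appear only in descriptive tables.
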